## Abstract

**Background:**

Self-reported knee pain is highly prevalent among adolescents. As much as 50% of the non-specific knee pain may be attributed to Patellofemoral Pain Syndrome (PFPS). In the short term, exercise therapy appears to have a better effect than patient education consisting of written information and general advice on exercise or compared with placebo treatment. But the long-term effect of exercise therapy compared with patient education is conflicting. The purpose of this study is to examine the short- and long-term effectiveness of patient education compared with patient education and multimodal physiotherapy applied at a very early stage of the condition among adolescents.

**Methods/Design:**

This study is a single blind pragmatic cluster randomised controlled trial. Four upper secondary schools have been invited to participate in the study (approximately 2500 students, aged 15-19 years). Students are asked to answer an online questionnaire regarding musculoskeletal pain. The students who report knee pain are contacted by telephone and offered a clinical examination by a rheumatologist. Subjects who fit the inclusion criteria and are diagnosed with PFPS are invited to participate in the study. A minimum of 102 students with PFPS are then cluster-randomised into two intervention groups based on which school they attend. Both intervention groups receive written information and education. In addition to patient education, one group receives multimodal physiotherapy consisting primarily of neuromuscular training of the muscles around the foot, knee and hip and home exercises.

The students with PFPS fill out self-reported questionnaires at baseline, 3, 6, 12 and 24 months after inclusion in the study. The primary outcome measure is perception of recovery measured on a 7-point Likert scale ranging from "completely recovered" to "worse than ever" at 12 months.

**Discussion:**

This study is designed to investigate the effectiveness of patient education compared with patient education combined with multimodal physiotherapy. If patient education and multimodal physiotherapy applied at an early stage of Patellofemoral Pain Syndrome proves effective, it may serve as a basis for optimising the clinical pathway for those suffering from the condition, where specific emphasis can be placed on early diagnosis and early treatment.

**Trial Registration:**

clinicaltrials.gov reference: NCT01438762

## Bagground

Self-reported knee pain is highly prevalent among adolescents [1,2]. Cross-sectional studies show that between 18.5 and 31% of adolescents report knee pain[1,3]. As much as 50% of the non-specific knee pain may be attributed to Patellofemoral Pain Syndrome (PFPS) [4]. The most frequently reported symptoms in PFPS are a diffuse peripatellar and retropatellar localised pain, typically provoked by ascending or descending stairs, squatting, cycling and sitting with flexed knees for prolonged periods of time [5].

The prevalence of PFPS has been reported across several age groups, with females having a prevalence approximately 1.5-3 times higher than males in athletic populations [6,7]. Among patients ranging from 10 to 49 years of age reporting to a sports medicine clinic, 70% of those diagnosed with PFPS were between the ages of 16 and 25 years [8]. The high prevalence of PFPS among young people is further supported by a recent study that examined 299 students aged 16-18 years [4]. They found that 25% of the students had experienced knee pain during the previous month. Of the students with knee pain, 50% were diagnosed with PFPS. Only two studies have investigated the incidence of PFPS within a closed population. Witvrouw et al (2000) followed 282 students of physical education and found that 9% developed PFPS during a two-year period [9]. Boling et al followed 1597 midshipmen for up to 2.5 years and found a significantly lower incidence of 3% [10].

There are a number of different treatment options for PFPS. Exercise therapy has been advocated as one of the cornerstones in rehabilitation of patients with PFPS. In the short term, exercise therapy appears to have a better effect than patient education consisting of written information and general advice on exercise [11] or compared with placebo treatment [12]. But the long-term effect of exercise therapy compared with patient education or flat insoles is conflicting. After 12 months of treatment, Collins et al. found no difference in pain or function between patients receiving multimodal physiotherapy (consisting of patellofemoral joint mobilisation, patellar taping, quadriceps muscle retraining, and education) or flat insoles [13]. Contrary to these results, van Linschoten et al. found a significant effect of supervised exercise therapy compared with patient education on self-reported pain levels after 12 months, but there was no positive effect on self-reported function or self-perceived recovery [11].

One possibility to improve short- and long-term outcomes is to initiate treatment early in the clinical course. Predictors of long-term outcome (> 52 weeks) indicate that a long symptom duration [14,15], higher age [16] and greater pain severity at baseline [14] are associated with poorer outcome. These prognostic factors suggest that an early initiation of treatment among adolescents may lead to a better long-term prognosis. The purpose of this study is to examine the short- and long-term effectiveness of patient education compared with patient education and multimodal physiotherapy applied at a very early stage of the condition among adolescents. We hypothesise a significantly larger proportion of completely recovered students at the 12 months follow-up in the patient education combined with multimodal physiotherapy treatment option compared with patient education alone.

## Methods

### Design

The study involves a single blind pragmatic cluster randomised controlled trial. The protocol conforms to CONSORT guidelines for non-pharmacological interventions [17] and is approved by the local ethics committee in North Denmark Region (N-20110020). All students below 18 years of age are required to give informed together with parental consent. Students aged 18 or 19 are allowed to give informed consent without parental consent.

### Patient selection

Four upper secondary schools were invited to participate in the study. All four schools accepted the invitation. All students (approximately 2500), aged 15-19 years, in the schools are invited to answer an online questionnaire as part of their physical education lessons. The students who report knee pain are contacted by telephone and offered a clinical examination by an experienced rheumatologist who evaluates which students are eligible to enter the study (Figure 1).

**Figure 1 F1:**
[figure not shown]
**Flowchart**. Subjects who are diagnosed with PFPS will be invited to participate in the study. 104 students diagnosed with PFPS will be cluster randomised into two groups based on which school they attend.

### Questionnaire

The online questionnaire contains questions regarding knee pain and general musculoskeletal pain, activity level, participation in sport, and quality of life measured by the EuroQol questionnaire (EQ5D). An EQ-5D score for all students will be calculated by using the official Danish time trade-off scores[18].

Localisation of pain is measured with a Pain Mannequin representing the entire body including the head. Students are asked if they have current pain in one or more of these areas. If they mark an area on the pain mannequin, they are asked how often they have felt pain in the area. The answer is divided into the following categories: rarely; monthly; weekly; more than one time per week; almost daily.

The physical education teachers will instruct the student in how to answer the questionnaire during a four-week period, starting two weeks after students have returned from summer holidays in 2011. After the questionnaires are filled out, they are automatically transferred to a secure server.

### Inclusion and exclusion criteria

Eligibility criteria are in line with a previous clinical trial [19]; age 15-19 years; insidious onset of anterior knee or retropatellar pain of greater than six weeks' duration and provoked by at least two of the following situations: prolonged sitting or kneeling, squatting, running, hopping, or stair walking; tenderness on palpation of the patella, or pain with stepping down or double leg squatting; and worst pain over the previous week of at least 30 mm on a 100 mm visual analogue scale (VAS). Exclusion criteria were concomitant injury or pain from the hip, lumbar spine, or other knee structures; previous knee surgery; patellofemoral instability; knee joint effusion; use of physiotherapy for treating knee pain within the previous year; or weekly use of anti-inflammatory drugs.

### Randomisation

Subjects who fit the inclusion criteria are offered to participate in the study. After all subjects have undergone a clinical examination and signed an informed consent, students are cluster-randomised into two intervention groups based on which school they attend. Cluster randomisation is chosen to minimise the bias that could be introduced if more than one student in each class is diagnosed with PFPS, but randomised to different treatment groups.

### Interventions

Both intervention groups receive written information and education delivered during one-to-one sessions with a physiotherapist.

### Information and education

One physiotherapist will carry out all patient education in the two clusters that are randomised to patient education only. The physiotherapist has previous experience in treating adolescents and PFPS and has more than two years of practical experience. The information and education is standardised and covers the topics of: why does it hurt: pain management; information on how to modify physical activity; how to return slowly to sports; how to cope with knee pain, and information on how to increase knee alignment during sit-to-stand, standing, walking, stair walking and bicycling. The patients will also receive this information in an eight-page leaflet. This session is expected to take approximately 30 minutes depending on the number of questions from the student or the parents.

### Information and education plus multimodal physiotherapy

The multimodal physiotherapy is carried out by two physiotherapists (one in each of the two clusters). Both have previous experience in treating adolescents and subjects with PFPS, and have more than two years of practical experience. The multimodal physiotherapy consists of patellofemoral soft tissue mobilisation, stretching of the muscles around the hip and knee, patellar taping, neuromuscular training of the muscles around the foot, knee and hip, quadriceps strength training for the knee and hip and instructions on home exercises [12,20]. The intervention is carried out on the school premises three times per week immediately after the end of class for a total of three months. Students are expected to vary greatly with regard to pain severity and level of function. To tailor the exercise therapy to the specific performance level of the student, all exercises are available in three or four different levels to enable progression (see Table 1). All students start with exercises at level one. Three general rules have been made to determine when progression of the exercises will occur:

**Table 1 T1:** the exact exercise, number of repetitions and external load will be determined by the physiotherapist.

Functional retraining exercises performed three times a week	•Sitting (isometric) • Sit-to-stand • Single step up • Stair walking • Single leg squat

Quadriceps muscle strengthening performed three times/week	• Inner range (open kinetic chain) • Mid range (open kinetic chain) • Weight-bearing

Hip abduction strengthening performed three times a week	• Side-lying hip abduction • Side-lying hip abduction with rubber band for resistance • Standing, hip abduction of the non-weight bearing leg • Standing, hip abduction of the non-weight bearing leg with rubber band between the ankles as extra resistance • Side-lying bridge • Side-bridge with hip abduction

Stretching	• Hamstring muscle stretches in sitting • Anterior hip structures stretch. Subjects in prone position, one hip externally rotated and with both the hip and knee flexed • Patellofemoral joint mobilisation and soft-tissue will be performed by the physiotherapist and taught so patient can perform this themselves

Patellar taping	• Combination of tilt, medial glide and fat pad unloading as necessary- the tape will be applied by the physiotherapist each training session

(1) Good quality of movement determined by the physiotherapist. 'Good quality' is defined as able to control hip, knee and foot alignment during exercises with both extra-slow and slightly faster than normal movement.

(2) Ability to perform the actual number of repetitions as defined in the training protocol.

(3) No self-reported increase in usual pain after the training session or the next morning.

To improve compliance, students are offered the opportunity to attend the supervised group training session at either 12:45, 13:45. or 15:15 to account for variation in the time the school lessons end. The training sessions are available Mondays, Wednesdays and Fridays.

### Patellar taping

Patellar taping based on the McConnell approach is included as it may reduce pain during exercise[21]. Non-rigid, hypoallergenic tape (Curafix H, Lohmann & Rauscher, Neuweid Garmany) will be used to reduce skin irritation while rigid zinc-oxide tape (Leuko P, BSN Medical, Hamburg, Germany) is used for the corrections of the patella. Taping corrections are applied in a predetermined order of anterior tilt, medial tilt, glide, and fat pad unloading until the participant**'**s pain is reduced by at least 50% [12]. Tape is only used if patients achieve a minimum of 50% reduction in pain measured with VAS during a two-leg squat immediately after application of the tape. Students are taught to independently apply the taping corrections and are instructed to reapply the tape daily and wear the tape during waking hours for the duration of the trial.

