#### Objective outcomes

A subgroup of 15 female students with PFPS from each cluster (a total of 60 students) is invited to participate in a sub-study investigating the effect of interventions on changes in neuromuscular function and isometric strength of the quadriceps. A person not involved in the treatment or diagnostics of the students randomly calls newly diagnosed subjects and asks them to participate. The students will undergo quadriceps strength measurements and two tests of neuromuscular function of m. vastus medialis and m. vastus lateralis before treatment and again after three months of treatment. Surface Electromyography (sEMG) is collected during two different conditions: stair walking and semi-squat at 90 degrees flexion at the knee joint. These measurements are carried out with the assessor blinded and before students are randomised. At three months follow-up, the same assessor tests all 60 students again. Before students are tested at three months follow-up, they are told not to reveal which intervention group they were assigned to. The assessor does not participate in any other parts of the study.

Bipolar surface electrodes (Ambu A/S, Neuroline, Ballerup, Denmark) are placed on the muscle bellies of m. vastus medialis (VM) and lateralis (VL) with an interelectrode distance of 22 mm. The electrode for VM is placed over the muscle belly 4 cm superior to and 3 cm medial to the superomedial patella border and orientated 55° to the vertical. The electrode for VL is placed 10 cm superior to and 6-8 cm lateral to the superior border of the patella and orientated 15° to the vertical [24]. The ground electrode is placed over the tibial tubercle.

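### The taping instruction covers the three-month sub-study test, where assessor blinding rests only on students not naming their group, and the tape condition at that test is not fixed

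*Protocol article*

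**What the plan says.** **Who is taped.** Taping is a component of one arm only: "The multimodal physiotherapy consists of patellofemoral soft tissue mobilisation, stretching of the muscles around the hip and knee, patellar taping" (Information and education plus multimodal physiotherapy). Within that arm it is conditional: "Tape is only used if patients achieve a minimum of 50% reduction in pain measured with VAS during a two-leg squat" (Patellar taping). The share expected to meet the condition is not given.

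**How long.** Students who use tape are "instructed to reapply the tape daily and wear the tape during waking hours for the duration of the trial" (Patellar taping). The supervised programme runs "three times per week immediately after the end of class for a total of three months", and questionnaire follow-up continues to 24 months (Self-reported outcome measurements).

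**When the sub-study is tested.** Quadriceps strength and surface EMG are measured "before treatment and again after three months of treatment" (Objective outcomes). On the first test the article says: "These measurements are carried out with the assessor blinded and before students are randomised". The same assessor retests all 60 students at three months.

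**How blinding is kept at the retest.** "Before students are tested at three months follow-up, they are told not to reveal which intervention group they were assigned to" (Objective outcomes). No other measure is described.

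**Where the assessor works.** "The electrode for VM is placed over the muscle belly 4 cm superior to and 3 cm medial to the superomedial patella border". The lateral electrode is also placed by distance from the patella, and the ground electrode sits on the tibial tubercle. A goniometer is secured around tibia and femur for stair walking.

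**The concern.** One section sets a treatment instruction that leaves a visible mark on the tested knee. Another relies on an assessor who should not know the arm. A request to stay silent cannot hide tape.

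Two things are at stake, both within the sub-study. First, the assessor's blinding may be lost at the only post-treatment measurement. Second, the measurement condition may be unequal: tape on some knees in one arm, none expected in the other, and no trial tape at baseline. The Strengths section hopes that these measures will help explain the mechanisms behind changes in pain and function. For that reading it matters whether a difference reflects three months of training or tape worn on the day.

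**Working it through.** **Step 1. Does the instruction reach the test day?** There are two readings of the phrase on duration.
- The whole trial, with follow-up to 24 months: the three-month test falls inside the taping period.
- The three-month intervention only: the test falls at its end. Whether tape is still worn then depends on the exact date, which the article does not fix.

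Under the first and more literal reading, tape is worn at the test. Under the second, the tape condition is undefined. Neither reading gives a stated, common condition.

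**Step 2. Would tape reveal the arm?** Tape is supplied in one arm. The Co-interventions section asks students to refrain from other treatments during the intervention period, so tape is not expected in the education arm. The assessor measures from the patellar border by hand. Tape that is present would be seen, and it would point to physiotherapy.

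**Step 3. Is baseline comparable?** Baseline tests precede randomisation, so no trial tape is worn. A taped student would be compared with an untaped earlier test and with untaped students in the other arm.

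**Step 4. The plan's own sub-study figure.** Inputs from Sample size: means 0.104 and 0.120, SD 0.02, power 80%. A two-sided alpha of 0.05 is assumed, since the article states alpha only for the primary outcome.

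n per group = 2 × (1.960 + 0.842)² × 0.02² / 0.016² = 24.5, so 25. The stated 25 is reproduced and is not in dispute.

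**Step 5. Sensitivity only.** The documents give no taped share f and no acute tape effect b, so both are assumed, and zero is a possible value of b. The shift in the between-arm difference is s = f × b. With 25 per arm, SE = 0.02 × √(2/25) = 0.00566.
- False-positive rate with no training effect: 1 − Φ(1.96 − s/SE) + Φ(−1.96 − s/SE).
- Power if the shift opposes a true 0.016: Φ((0.016 − s)/SE − 1.96).

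| f (assumed) | b (assumed) | s | False-positive rate | Power if opposing |
|---|---|---|---|---|
| any | 0 | 0 | 5.0% | 80.7% |
| 0.25 | 0.004 | 0.001 | 5.4% | 75.5% |
| 0.5 | 0.008 | 0.004 | 10.9% | 56.4% |
| 1.0 | 0.008 | 0.008 | 29.3% | 29.3% |

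The rows run from no effect to a material one. They show why the condition should be fixed in advance; they are not evidence that tape shifts sample entropy.

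**The case against.** The strongest reply is that this argues from silence. A journal article condenses the full protocol, and test-day preparation is the kind of detail it leaves out. Nothing says that testing is done with tape on. That stands as a caution: tape at the measurement is an inference. It does not dispose of the point, because the article states both a wearing instruction that covers the test and the safeguard meant to protect blinding there, and the two do not fit together.

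The following also stands:
- A reader might infer that the whole physiotherapy arm arrives taped. The 50% rule excludes this. An unknown fraction is taped, and how many still tape at three months is also unknown.
- A reader might infer a quantified confounding effect. The article says only that tape may reduce pain during exercise. It links tape to none of the sub-study outcomes, in size or direction.
- The assessor has limited discretion. The dynamometer is strapped, the command is standardised, entropy is computed and onset is found by an automatic algorithm. Electrode placement by hand and spoken encouragement leave some room for influence.
- Taping is part of the package in a pragmatic trial, so a comparison that includes tape is legitimate. That would be a reason to state the condition, and it would not restore blinding.

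**Conclusion.** The point holds for the three-month sub-study test. Followed as written, the taping instruction can reveal allocation to an assessor meant to be blinded. It also leaves the tape condition unequal between arms and different from baseline. This rests on the plain reading of the duration phrase and on no removal step existing in the full protocol, which is not shown.

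The size of any bias is unknown and cannot be derived from the documents. The scope is the 60-student sub-study. A reader might extend the worry to the trial's main result, but the 12-month primary outcome is the student's own rating and does not involve this assessor. The matter should be settled before the three-month tests, and it does not threaten the main comparison.

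**What to change.** Reconcile the Patellar taping and Objective outcomes sections:

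1. State in Objective outcomes that the sub-study strength and EMG tests are done in the same untaped condition in both arms and at both visits.
2. Put one identical instruction in the SMS reminder already sent the day before appointments, to all sub-study students regardless of arm. They then remove any tape themselves before meeting the assessor.
3. Do not give a tape check to the physiotherapist who hands out the questionnaires. That person is independent of treatment and answers students' questions while the primary outcome is collected; seeing tape would reveal the arm there.
4. Optionally, have the assessor record a guess of allocation after each three-month test, so that blinding can be reported. This would also pick up other routes to unblinding, such as knowing a student's school when allocation is by school, which removing tape does not close.

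The cost is a sentence or two in the sub-study procedure and one line in an existing message, with no extra staff. The downside is a short time without tape around one test. This sets a measurement condition only; the taping regimen is otherwise left to the investigators.
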